### Measurement of outcomes

We don’t expect the intervention to have adverse effects at local and individual level. The primary outcome is neonatal mortality (deaths in the first 28 days per 1000 live-births), Secondary outcomes include maternal mortality (deaths of a pregnant women or within 42 days of cessation of pregnancy from any cause related to the pregnancy or its management, but not from accidental causes), stillbirth, miscarriage (cessation of a presumptive pregnancy before 28 weeks of gestation), preterm birth, low birth weight, maternal morbidities such as pregnancy complications or near miss as an alternative, frequency of antenatal care visits, accessibility to skilled birth attendants for delivery, referral for identified complications, utilization of postpartum care, and status of initiating breastfeeding. We will use International Classification of Diseases version 9 definition of stillbirth for the study settings [20].

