## Background

Every year, approximately 290,000 women die due to pregnancy and childbirth, and 99% of maternal mortality occurring in the developing world. Bangladesh is one of those developing countries with high maternal mortality ratio (MMR), standing at 170 per 100,000 live births [1]. Although it has become a lower-middle income country with economic growth and achieved various targets of the Millennium Development Goals (MDGs), the target on reduction of maternal mortality and utilization of related obstetric and reproductive services provided by skilled health personnel remains unmet, and the progress in reduction of neonatal mortality ratio (NMR) lag behind that in the reduction of infant and under-five mortalities, with the proportion of neonatal mortality accounting for 39% of under-five mortality in 1991 increasing up to 60% in 2012 [2]. Reduction of maternal and neonatal mortality therefore remains as a crucial issue for the Sustainable Development Goals (SDGs), which aims to reduce MMR to less than 70 per 100,000 live births and NMR to less than 12 per 1000 live births in all over the world [3].

Accessibility to good-quality health care at both community and referral level is crucial to reduce maternal and neonatal deaths. In rural Bangladesh, where the home delivery by traditional birth attendants accounts for approximately 85% of all child birth [4], antenatal care visits as recommended by the World Health Organization (WHO), childbirth attended by skilled health personnel, and timely referral for emergent maternal and neonatal complications urgently need to be improved. As proved in previous studies, a participatory community-based intervention is effective to improve birth outcomes with low-cost, and realistic to achieve the progress for the rural area [5, 6].

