### Study procedures

The study period includes one-year recruitment of participants and follow-up during pregnancy and the neonatal period. The study starts from February 01, 2017 when we start to enroll the participants, and is expected to finish on August 30, 2018 when all participants go through the neonatal period, four weeks after giving birth. All eligible pregnant women living in the selected villages for the intervention and the control will be recruited right after the allocation. Our trained staffs will visit each household to collect the baseline and the end-of-point data on the pregnancy by using a structured questionnaire at the enrolment and the end of four weeks after delivery or cessation of pregnancy, the ending point of the participation, respectively. In the survey, variables related to the expected outcomes as describe below as well as demographical and socioeconomic characteristics and indicators on knowledge and practices will be obtained. A code to identify each participant during the study period will be created.

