In the intervention group, a short message will be sent to the participants to welcome them and the printed version of MCH handbook will be provided to the participants to the intervention. Our trained staffs together with CHWs will build a close linkage with pregnant women and their family members by using mobile short messaging and audio system. To monitor their conditions and make a record, the staffs will send a short message to the participants at the frequency of every two weeks and to alert them to visit for antenatal care in advance, and if necessary, also visit their home to talk with the participants face-to-face. As the coverage of at least four visits of antenatal care recommended by WHO is low in rural Bangladesh, our first target will to improve the number of antenatal care visits. Then, text messages on essential health items including perinatal care, including antenatal care visit, nutrition during pregnancy, intake of iron tablet and folic acid, work, rest and daily activities, husband and families’ support during pregnancy and lactating period, danger signs, list of skilled birth attendants and hospitals, signs of labor, postnatal care, neonatal care, breastfeeding, and family planning, will be edited to be user-friendly and sent accordingly to each participant appropriate to their gestational age and location of the residence. For those cannot read, our staffs will use phone call instead of short messages. For those participants who don’t own a mobile, we will ask the neighbors or the relatives living closely to them to share the mobile where messages could be sent, because of the close liaison in the rural community. Every two month, the enrolled pregnant women and their families and CHWs will be organized to a community meeting by the mobile network, for face-to-face health education, consulting / advices and ANC during pregnancy. Data on health status during pregnancy, childbirth and postpartum, utilization of related healthcare services at community and facility levels, opinions of the participants and maternal and neonatal outcomes will be collected by using the mobile network and home visiting. On the other hand, in the control group, a routine care will be provided usually, but no intervention will be implemented. Related data will be collected by home visiting during the study period and the end-of-point survey.

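### Maternal mortality is defined to 42 days after pregnancy ends, but planned follow-up stops at four weeks, so days 29–42 have no planned data collection

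*Protocol article*

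**What the plan says.** Measurement of outcomes in the protocol article lists maternal mortality first among the secondary outcomes and defines it as "deaths of a pregnant women or within 42 days of cessation of pregnancy from any cause related to the pregnancy" or its management, with accidental causes excluded.

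Study procedures sets the observation period in three statements, all pointing to four weeks:
- The study period is "one-year recruitment of participants and follow-up during pregnancy and the neonatal period".
- The closing household questionnaire takes place at "the end of four weeks after delivery or cessation of pregnancy, the ending point of the participation".
- The study "is expected to finish on August 30, 2018 when all participants go through the neonatal period, four weeks after giving birth".

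The same section describes further data collection without giving any contact after week four. In the intervention group, "maternal and neonatal outcomes will be collected by using the mobile network and home visiting". In the control group, "Related data will be collected by home visiting during the study period and the end-of-point survey".

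The primary outcome has a window that fits this schedule: "The primary outcome is neonatal mortality (deaths in the first 28 days per 1000 live-births").

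**The concern.** The window in the definition is longer than the window of observation. A woman alive at the four-week questionnaire leaves the study with two weeks of the defined risk period still to run. If the plan is followed as written, the result will carry a 42-day definition but rest on information to about day 28.

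What is at stake is the meaning of the reported figure. Truncation can only lower the count of deaths. The Background frames the trial around a national maternal mortality ratio "standing at 170 per 100,000 live births" and the development goal of fewer than 70, so readers will be inclined to set the trial's figure beside a 42-day ratio. An analysis plan cannot repair this later, because the missing information is never collected.

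**Working it through.** The document gives no figure for this point to reproduce. The check compares the windows, counts dates, and sets a scale for the number of events.

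**Inputs**
- Outcome window: 42 days after the pregnancy ends (Measurement of outcomes).
- Last questionnaire and end of participation: four weeks, i.e. 28 days (Study procedures).
- Study end: August 30, 2018 (Study procedures).
- Maternal mortality ratio: 170 per 100,000 live births (Background).
- Total sample: 3000, in three groups of 1000, each made up of 500 in each of two areas (Abstract).
- Assumed loss to follow-up: 25% (Statistical analysis).

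**Step 1: gap between the windows.** 42 − 28 = 14 days, i.e. days 29–42. As calendar time this is 14/42 = one third of the postpartum part of the definition. The definition also covers pregnancy itself, which is under observation from enrolment.

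**Step 2: is the gap closed elsewhere?** The mobile and home contacts in Study procedures carry no schedule beyond week four, and the same section ends participation at that point. The article describes no day-42 contact, death register or record linkage.

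**Step 3: calendar.** Counting back from August 30, 2018:
- 28-day follow-up is complete for deliveries up to August 2, 2018 (August 30 − 28 days).
- 42-day follow-up is complete only for deliveries up to July 19, 2018 (August 30 − 42 days).
- Keeping August 2 as the last delivery date would require field work to September 13, 2018 (August 2 + 42 days).

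**Step 4: scale.** Taking one live birth per enrolled woman as an assumption:
- Full sample: 3000 × 170/100,000 = 5.1 maternal deaths expected.
- After loss: 3000 × 0.75 = 2250, and 2250 × 170/100,000 = 3.8.
- Per group of 1000 before loss: 1000 × 170/100,000 = 1.7.

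**Step 5: size of the understatement.** This would be the expected deaths multiplied by the share falling on days 29–42. The document does not give that share, so the product cannot be computed.

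**The case against.** The strongest reply is that little depends on this. Maternal mortality is one of about a dozen secondary outcomes, the primary outcome matches the four-week visit exactly, and a risk ratio built on 4 or 5 deaths says almost nothing whether or not the last two weeks are covered. That stands, and it limits the severity.

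It can also be said that field work continues to August 30, 2018, so staff are still in the area past day 42 for women who deliver early and may hear of later deaths. That is possible but unplanned. It cannot serve as ascertainment, and within the stated dates it is not available for women delivering after July 19, 2018.

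Condensation for a journal is not an answer, because the article states both windows and they disagree.

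Several stronger readings are tempting, and the document does not support them:
- **The outcome is unobservable.** Deaths in pregnancy and up to day 28 lie within follow-up. Only the full 42-day definition is not covered.
- **A third of the deaths, or a fifth, would be lost.** One third is calendar time, not risk. A fifth (1 of 5.1) presumes that one death falls in the gap, which nothing in the document shows.
- **The comparison is biased because late news arrives only in the intervention arm.** The four-week end applies to every arm, so truncation alone does not obviously distort the risk ratio. Controls are also visited at home. Mobile data collection is described only for the intervention group and field staff are not masked, so unequal incidental reporting is conceivable but not established.
- **Postpartum care is cut short in the same way.** That outcome is given no window, so measuring it to four weeks contradicts nothing.
- **The trial plans a comparison with the national ratio.** The ratio and the development target appear as background only.

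**Conclusion.** The two sections contradict each other, and the plan as written would yield maternal mortality to about day 28 reported under a 42-day definition. The last 14 postpartum days have no planned data collection for any woman. The figure may be too low by an amount that cannot be estimated from the document, and it should not be set beside a 42-day ratio.

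The practical weight is modest. With about 4 to 5 deaths expected across all arms, the comparison between arms is uninformative under either window, and 28-day neonatal mortality is untouched. This is a should-fix. The contradiction rests only on the two stated windows and on no later source being described. The expected count rests on applying the national ratio to enrolled women, with one live birth each.

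**What to change.** Reconcile Measurement of outcomes with Study procedures in one of two ways.

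1. **Align the definition with the observation.** Define and label the outcome as maternal death in pregnancy or within 28 days of its end, and do not compare it with the 42-day ratio. This is a change of wording only. The price is an outcome that is not the 42-day measure.

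2. **Align the observation with the definition.** Ascertain the mother's vital status at or after day 42, identically in all arms, by timing the end visit at day 42 or later and recording at that visit the infant's status at day 28 and any date of death. The number of visits stays the same. The costs are slightly longer recall for the primary outcome, in a trial that already acknowledges its reliance on participants' reports, and a closing date about two weeks later (September 13, 2018, if deliveries up to August 2 are kept). If the longer recall is unwelcome, the four-week visit can stay and a brief vital-status check at day 42 can be added in every arm, at the price of one more contact per woman.

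The choice should be made before field work closes, because days 29–42 may not be recoverable afterwards.

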### Quality control

A local NGO, Bridge of Community Development Foundation will take responsibility to maintain the quality of the implementation and data collection. The local Program coordinators will train the field staffs at the beginning of the project and provide enough education and refreshing training for the standard control as they are doing. The recruited community health workers, birth attendants in the community and field staffs will also receive refresh training from the maternal and child health experts and the health professionals working the referral level facility. They will get idea about their role in the community and necessary knowledge to provide essential care, identify the complications and implement referral to the upper-level facilities. At the end of the field study, we will provide an appropriate incentive to those participants who fully attend without any missing information, in order to reduce the drop-out and missing data and to express our thanks for their cooperation.

Data from the field study, including the questionnaire, the MCH handbook and other data collected from the study settings will be double-entered in an electronic database. The local project coordinators, local survey staffs and data managers will work together for the quality control.

## Discussion

The intervention incorporating the home-based health records with the mobile health network aims to improve health seeking behaviors of pregnant women living in rural Bangladesh, for better maternal and neonatal health outcomes. The innovative intervention package, the combination of mobile phone network and MCH handbook can be relatively complemented and is expected to maximize both advantages in terms of knowledge dissemination, promotion of communication, preservation of home-based health records, and facilitation of continuum of perinatal care. To our knowledge, our proposed study will be the first one to measure the impact of such a combined approach. The cluster-randomized research design is robust to evaluate the effects of the proposed intervention and to provide insight to maternal and neonatal issues in the field.

We recognize that the high proportion of home-based delivery practiced by less skilled personnel in particular in the rural area remains as a bottleneck against achievement of the targets related to maternal and neonatal care in health-related SDGs, which figures are not comparative, but rather absolute. Therefore, as the fundamental step, to improve health seeking behaviors during pregnancy and postnatal period, especially utilization of antenatal care and skilled personnel and timely detection and referral in case of emergency is crucial for the achievement. Although tremendous efforts are necessary in both the demand and the supply side and there is still a long way towards achievement of related targets in SDGs, the project doesn’t have resources to improve service delivery intensively at health facilities, the supply side. Rather, the intervention focus on improving of utilization of antenatal care and skilled personnel, raising of health awareness of pregnant women and their families and strengthening the referral system by the mobile network, and effective link between the primary level and the referral level is expected to contribute to capacity building of CHWs and birth attendants.

In Bangladesh, the Ministry of Health and Family Welfare has started a nationwide project to increase health awareness by broadcasting text messages to all mobile phone numbers in 2007 [7]. On the other hand, the quality of the implementation and the impact of the SMS health messages on population health remain unknown. For pregnant women, while there is the mobile phone-based short message pregnancy advice system and those living remote villages are theoretically able to receive useful prenatal advice, the one-way operation may limit communication between healthcare providers in the community (CHWs and birth attendants) and pregnant women, and consequently the efficiency of the project. In other words, we concern that the potential of the mobile network may not be maximized. In our study, both text and audio messages will be fully applied to meet the individual needs and to boost communication among various stakeholders in the community. We take those don’t have mobile phone and those cannot read into consideration as well. A community-based approach, rather than a top-down governmental approach, will take the advantage of the close liaison of local members in the rural community of the country and assess the effectiveness of the intervention based on the scientific methodologies.

The study have some limitations due to relying on participants’ report, potentially causing bias of data. First, the pregnancy weeks will be reported by the participants as a precise detection by ultrasound is not available in the study settings. Moreover, cost data also rely on participants’ report. Health seeking behaviors depend on their husband’s decision. Nevertheless, by integrating and empowering the network at the communities, the proposal study is expected to improve health seeking behaviors including utilization of antenatal care and contribute to better maternal and neonatal health outcomes.

## Conclusions

This will be one of the first implementation study among women to improve the maternal and neonatal care using the mobile messages and home-based health record in Bangladesh, aiming to provide an innovative solution for MCH related SDGs. Know-how on the integration of mobile network and home-based health record would be disseminated and applied in other health program with successful experience.

## Abbreviations

ANC: Antenatal care
CHWs: Community Health Workers
MCH: Maternal and Child Health
MDGs: Millennium Development Goals
MMR: Maternal Mortality Ratio
NMR: Neonatal Mortality Ratio
RCT: Randomized Controlled Trial
SBAs: Skilled Birth Attendants
SDGs: Sustainable Development Goals
WHO: World Health Organization
